### Statistical analysis

2.7

Statistical analyses were performed using SAS version 9.3 (SAS Institute Inc., USA) and included baseline characteristics, efficacy, and safety outcomes. A p-value of < 0.05 was considered statistically significant. The efficacy analysis will follow the intention-to-treat (ITT) principle. The Full Analysis Set (FAS) includes all randomized patients, excluding those who severely violated the inclusion criteria or did not receive any assigned treatment. Baseline characteristics will be analyzed within this set to assess comparability. The Per-Protocol Set (PPS) includes patients who completed the planned treatment regimen, whereas the Safety Set (SS) consists of patients who received at least one dose of the study treatment and underwent safety evaluation. Efficacy analysis will be primarily applied to the FSA and PPS. Safety evaluations will be performed using the SS.

For primary and secondary outcomes, continuous data will be analyzed using the t-test or Mann-Whitney U test; categorical data will be assessed using the Chi-squared test or Fisher’s exact test; and ordinal data will be evaluated using the Mann-Whitney U test. To account for potential center effects in this multicenter trial, analyses will be stratified by study site. Efficacy will be evaluated using the Cochran-Mantel-Haenszel (CMH) test to adjust for inter-center variability.

If baseline characteristics between groups are imbalanced, confounding factors that are difficult to control or unmeasured may be included as covariates in an analysis of covariance (ANCOVA) or logistic regression model. Between-group differences in efficacy will be assessed using least-squares means (LSMEANs) and their 95% confidence intervals to minimize the impact of confounding factors.

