#### Inclusion criteria

2.2.2

Patients who eligible for the trial must fulfill all of the following criteria at the time of randomization:

Participants are aged between 18 and 75 years.A confirmed diagnosis of ACS within 2 to 12 weeks prior to enrollment, with hemodynamic stability and absence of acute cardiovascular complications.Participants exhibited persistent symptoms of depressed mood or anhedonia for at least 2 weeks, with 17 < HAMD-17 ≤ 24All eligible participants must provide written informed consent.

Note:

Depressed Mood: The affective manifestation persists nearly daily for the majority of waking hours, manifesting through either subjective affective experience (e.g., persistent feelings of sadness, emotional emptiness, or hopelessness) or objective behavior observed by others (e.g., frequent episodes of tearfulness).Anhedonia: Present almost daily occurrence for most of the day. This involves a significant decrease in interest or pleasure in all or almost all activities (which can be either self-reported or observed).

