#### Termination and dropout of trial patients

2.2.4

Patients who fail to meet the inclusion criteria or fulfill any exclusion criteria.Patients with poor protocol compliance or who withdrew prematurely from the trial.Patients with incomplete medical records that hinder the evaluation of efficacy and safety.Patients whose condition deteriorated rapidly during the study, including those with acute cardiovascular events or malignant neoplasms.Patients whose depression worsens during the trial (HAMD-17 score >24 for over two weeks) or who display suicidal ideation.Patients with serious adverse events during the trial.Voluntary withdrawal by the patient.

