#### Blinding

2.3.2

This study adopts a double-blind design. The first level blinding corresponds to the group codes linked to medication numbers (Group A, Group B), while the second level pertains to the treatments assigned to each code (SGJY group or placebo control group). Both levels of blinding will be documented by statisticians independent of trial analysis. Two sealed copies of the blinding records will be maintained separately by the principal research center. These blinding records must remain unopened throughout the study period. The first unblinding for the statistical analyst will conduct after data lock, and the second after completion of the statistical analysis. Emergency envelopes may only be opened in the event of a medical emergency (serious adverse event, rapidly deteriorating condition). Each envelope will contain designated fields for the signature, date, and reason for unblinding by the person who opens it. Cases withdrawn due to therapeutic reasons should not be unblinded. The unblinded case materials must be kept intact.

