#### Data locking and review

2.6.3

Upon completion of data entry, the principal investigator and statistical analysts will lock the data while remaining blinded, after which no further modifications will be allowed. A line-by-line verification will then be conducted to review the entries made by both data entry personnel. A random sample of CRFs will be selected and cross-checked against the data in the EDC system to ensure consistency with the original source data.

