### Quality control

2.8

Researchers must strictly follow the study protocol and comply with standard operating procedures. All clinical observations and findings must be verified to ensure the effective implementation of quality control and quality assurance systems throughout the study. Quality control measures must be implemented at every stage of data processing to ensure the reliability and accuracy of the data.

Prior to study initiation, all participating researchers must undergo comprehensive training, including guidance on relevant data, operational procedures, and assigned responsibilities. Given that the study involves assessments using scales related to anxiety and depression, all researchers must be trained by a psychiatrist, and qualified professionals in psychological assessment must be included in the research team. This ensures consistency in clinical data collection and guarantees that all data are recorded objectively, accurately, and truthfully in the medical records and CRFs. Throughout the study, monitors from the lead research institution will conduct regular audits of source clinical data at study sites to ensure strict adherence to the study protocol. If a subject’s treatment regimen is modified during the study, investigators must record the details and reasons for the change and continue follow-up as planned. During data analysis, the principal investigator and statistical experts will allocate each subject to the appropriate analysis set.

Researchers should foster participant confidence in the treatment and maintain effective communication to ensure a clear understanding of the study requirements, thereby improving adherence. Participant adherence will be monitored using the medication count method. Before each medication dispensing, remaining study drugs and empty packaging will be collected. Adherence will be calculated as follows: [(prescribed amount - unused amount)/prescribed amount] × 100%. Good adherence: 80%-120%, Poor adherence: <80%.

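### The Full Analysis Set removes randomised patients for severe eligibility breaches, which is not the promised ITT analysis, and set membership is decided during the analysis, after the A/B codes are released

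*Protocol article*

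**What the plan says.** Section 2.7 (Statistical analysis) states: "The efficacy analysis will follow the intention-to-treat (ITT) principle". The next sentence defines the FAS as all randomised patients, "excluding those who severely violated the inclusion criteria or did not receive any assigned treatment". The efficacy populations are then named: "Efficacy analysis will be primarily applied to the FSA and PPS" (FSA is evidently a misprint for FAS). The per-protocol set is limited to patients who completed the planned treatment.

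Section 2.8 (Quality control) says who decides membership and when: "During data analysis, the principal investigator and statistical experts will allocate each subject to the appropriate analysis set".

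Two sections bear on what is known at that point. Section 2.3.2 (Blinding): "The first unblinding for the statistical analyst will conduct after data lock, and the second after completion of the statistical analysis". The first level is the A/B group code, the second is which code is SGJY. Section 2.6.3 (Data locking and review): "the principal investigator and statistical analysts will lock the data while remaining blinded", with no changes allowed afterwards.

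Section 2.2.2 requires that patients "must fulfill all of the following criteria at the time of randomization". The first item of section 2.2.4 (Termination and dropout of trial patients) reads: "Patients who fail to meet the inclusion criteria or fulfill any exclusion criteria". Section 2.2.5 asks that dropouts be kept in contact, assessed where feasible and fully documented.

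**The concern.** An intention-to-treat analysis keeps every randomised patient in the group to which that patient was assigned. The FAS as defined can lose patients who were randomised and treated, and no other set restores them. The label and the definition therefore conflict within two consecutive sentences.

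The grounds for removal make this more than a naming problem. Severity is a matter of degree, and it is judged after randomisation. The entry criteria include clinician-judged items (persistent depressed mood or anhedonia, and a HAMD-17 range). Whether a breach is noticed and called severe may depend on how the patient fared. If the judgement is made with complete outcomes and group codes available, the main efficacy set is open to post-randomisation selection, and the comparison no longer rests on randomisation alone.

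**Working it through.** **1. The plan's own figure.** Inputs from section 2.3.3: response 45.7% (control) and 69% (SGJY), two-sided alpha 0.05, power 80%, 1:1. With unpooled variance,

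n = (1.960 + 0.842)² × (0.457 × 0.543 + 0.69 × 0.31) / (0.69 − 0.457)² = 7.849 × (0.2482 + 0.2139) / 0.05429 = 66.8, so 67 per group. 

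67 × 1.1 = 73.7, so 74 per group and 148 in total. The plan's numbers are reproduced.

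**2. The order of events as written.**
- Data are locked blind (2.6.3). This freezes data values; nothing there says that it freezes set membership.
- The statistical analyst receives the A/B codes (2.3.2).
- The analysis runs, and during it patients are allocated to sets (2.8).
- Treatment identity is released (2.3.2).

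Allocation to sets therefore falls between the two unblindings. Codes together with outcomes show which group is doing better, though not which group is SGJY.

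**3. Effect of removals on the primary test.** Control is set at 34/74 (45.9%), the nearest count to 45.7%. The test is the pooled z-test, equivalent to Pearson chi-square without continuity correction:

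z = (a/n₁ − c/n₂) / √[p̄(1 − p̄)(1/n₁ + 1/n₂)], with p̄ = (a + c)/(n₁ + n₂).

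For 45/74 vs 34/74: p̄ = 79/148 = 0.534, difference 0.1486, standard error 0.0820, z = 1.81, p = 0.070.

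| SGJY | Placebo | Removed | p |
|---|---|---|---|
| 45/74 | 34/74 | none | 0.070 |
| 45/73 | 34/74 | one SGJY non-responder | 0.056 |
| 45/74 | 33/73 | one placebo responder | 0.058 |
| 45/72 | 34/74 | two SGJY non-responders | 0.045 |
| 45/73 | 33/73 | one of each | 0.047 |
| 44/74 | 34/74 | none | 0.100 |
| 44/72 | 34/74 | two SGJY non-responders | 0.066 |
| 44/71 | 34/74 | three SGJY non-responders | 0.053 |
| 44/70 | 34/74 | four SGJY non-responders | 0.042 |
| 46/74 | 34/74 | none | 0.048 |
| 51/74 | 34/74 | none (about the planned effect) | 0.005 |

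At 74 per arm, then, 45 responders need two favourable removals and 44 need four; 46 are significant without any. With 67 analysed per arm, 42/67 vs 31/67 gives p = 0.056, and one removal (42/66) gives 0.044.

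**4. How often this could matter.** Exact binomial enumeration gives the probability that a non-significant result could be made significant by the most favourable removals:

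| n per arm, true rates | one removal | two removals |
|---|---|---|
| 74, 45.7% vs 69% | 0.8% | 4.0% |
| 74, 45.7% vs 60% | 0.2% | 6.6% |
| 74, no effect (45.7% in both) | 0.1% | 1.3% |
| 67, 45.7% vs 69% | 4.5% | 7.3% |

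In the no-effect row these add to a 2.9% chance of significance in favour of SGJY without removals.

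**5. Power if nobody is removed.** With all 74 per group analysed at the planning rates, the pooled formula gives 82.4%. Keeping these patients needs no larger trial, provided those rates hold in all of them.

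**The case against.** The strongest reply is that blinding makes one-sided selection unlikely. The trial is double-blind, the lock is blind, and treatment identity is withheld until the analysis is complete. The table's removals are chosen to favour SGJY. If two violators were drawn at random from 148, the chance that both were among the 29 SGJY non-responders would be (29/148) × (28/147) = 3.7%. Closer scrutiny of poor responders would, under blinding, apply to both arms. This stands as a limit on the size of the risk. It does not remove the risk, because section 2.8 puts the allocation after the A/B codes are released. Only the statistical analyst is said to receive those codes, but statistical experts are among those who allocate.

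A second reply concerns the test. Section 2.7 specifies a site-stratified CMH test, and the figures here are unstratified. For 45/72 vs 34/74 a continuity correction gives p = 0.066, while Fisher's exact test gives 0.048. The exact crossing point therefore depends on the test; the definition of the set does not.

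Three stronger readings may tempt a reader, and the documents do not support them:
- *One or two exclusions decide the primary result.* At 74 per arm and about the planned control rate, two are needed, and only from a result already close to 0.05.
- *Sections 2.2.2, 2.2.4 and 2.7 define three different analysis populations.* Only 2.7 defines analysis sets; the others govern eligibility and termination. Nothing says that a terminated patient leaves the FAS, and sections 2.2.5 and 2.8 ask for continued contact, feasible assessments and follow-up to the end of the study.
- *The missing definition of severity is itself an error.* A statistical analysis plan, not shown here, may supply one. It still would not return the removed patients to the FAS.

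**Conclusion.** The point holds in limited form. The protocol article promises intention to treat, fixes a main efficacy set that is not intention to treat, and schedules membership decisions for a time when outcomes and group codes are available. This should be corrected, but it does not threaten the trial at its planned effect.

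The exposure is confined to near-threshold results: at the planning rates and 74 per arm, about 4% of trials could be turned by two fully favourable removals. That is an upper bound for two removals, since it assumes that they are the most favourable possible. The figures also assume response counts near the planning rates and an unstratified test, because site-level rates are not given. Leaving out never-dosed patients is a lesser departure in a double-blind trial and matters here mainly for the label.

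**What to change.** - Define the FAS as all randomised patients who took at least one dose, analysed as randomised, with no removal for eligibility breaches. If never-dosed patients are left out, call it a modified ITT set.
- Report the result without eligibility violators only as a sensitivity analysis.
- Change section 2.8 so that set membership is fixed and documented before the A/B codes are released.
- Reconcile the first item of section 2.2.4 with sections 2.2.2, 2.2.5 and 2.7, so that it is clear that patients found ineligible after randomisation still contribute outcome data. This concerns data for analysis only; no change to clinical management is proposed.

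The cost is a few sentences and slight dilution of the effect by a few ineligible patients. No extra recruitment is needed if the planning rates hold.

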#### Random allocation

2.3.1

All eligible patients who provide informed consent will be randomly assigned in a 1:1 ratio to either the control group or the SGJY group. Stratified block randomization will be used, with clinical research center as the stratification factor. A statistician independent of trial analysis will generate the randomization table using SAS software, based on the stratification factor and allocation ratio. The number of blocks, block length, random seed parameters, and other confidential data will be sealed along with the randomization table in an opaque envelope, which will serve as the First unblinding record.

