This study has several limitations. First, the treatment period is limited to 12 weeks, with a follow-up visit scheduled 36 weeks after the end of treatment. This relatively short follow-up duration may restrict the ability to fully capture the occurrence of MACCE. This limitation elevates the risk of false-negative conclusions and consequently impairs the accuracy of evaluations regarding whether patients with ACS actually benefit from antidepressant treatment. However, previous studies have shown that biomarkers such as GDF15 and sCD40L are reliable surrogate indicators of long-term prognosis. Consequently, this trial may offer valuable insights into the potential role of SGJY in improving the prognosis of ACS. Second, CPET will be conducted by different operators across the five centers—a factor that introduces the risk of measurement variability and potential bias. Differences in test procedures, equipment calibration, or data interpretation among operators may compromise the accuracy of results and subsequent assessments of the intervention’s efficacy. To mitigate this risk, we implemented a stringent set of SOP for all CPET assessments. Furthermore, all operators and assessors received centralized, uniform training on operational and analytical protocols before the trial commenced. Third, the use of clinician-rated scales to evaluate treatment efficacy may lead to subjective bias. To ensure the reliability of the evaluation results, all researchers will undergo standardized training provided by psychiatrist before the study get started. In addition, objective biomarkers (including inflammatory cytokines, relevant proteins, HPA axis-related hormones, and BDNF) will be incorporated to support efficacy evaluation. Fourth, The use of Consensus criteria in this study may introduce over-diagnosis bias by potentially including patients who meet diagnostic criteria for Major Depressive Disorder (F32.0/F32.1) or Organic Depressive Disorder (F06.32). To address this limitation, we will perform stratified analyses by diagnostic subgroup to assess result reliability.

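### The tests named for continuous outcomes carry no centre term, although randomisation is stratified by centre and the same paragraph promises site-stratified analyses; used as written, they are conservative to the extent that centres differ

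*Protocol article*

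**What the plan says.** All references are to the protocol article.

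- **Randomisation (2.3.1):** "Stratified block randomization will be used, with clinical research center as the stratification factor". Section 2.1 lists five centres.
- **Tests for continuous data (2.7, second paragraph, covering primary and secondary outcomes):** "continuous data will be analyzed using the t-test or Mann-Whitney U test".
- **Centre (same paragraph):** "To account for potential center effects in this multicenter trial, analyses will be stratified by study site", followed by "Efficacy will be evaluated using the Cochran-Mantel-Haenszel (CMH) test to adjust for inter-center variability".
- **Model-based analysis (2.7, third paragraph):** if baseline characteristics are imbalanced, confounders "may be included as covariates in an analysis of covariance (ANCOVA) or logistic regression model". Centre is not listed. The paragraph continues: "Between-group differences in efficacy will be assessed using least-squares means (LSMEANs) and their 95% confidence intervals".
- **Expected centre differences (3 Discussion, limitations):** on cardiopulmonary exercise testing (CPET), "Differences in test procedures, equipment calibration, or data interpretation among operators may compromise the accuracy of results". Standard procedures and central training are given as mitigation.

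The primary outcome (2.5.2.1) is a response proportion, so it is binary. The continuous outcomes are most of the list in 2.5.2.2: the SAQ, PHQ-9, HAMA, GAD-7, DARS, SF-36 and MoCA scores, the CPET measures, cytokines, HPA-axis hormones and BDNF.

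**The concern.** An ordinary t-test or Mann-Whitney test compares two arms without regard to centre. An analyst cannot run the named test and also honour the stratification sentence, and the article does not say which gives way for continuous data.

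The choice has a known statistical consequence. Balancing the arms within each centre removes centre differences from the true variance of the arm comparison. The two-sample standard error does not know this and still counts the between-centre spread as noise. Intervals are then wider than they need be and the test rejects too rarely under the null. What is at stake is precision on the secondary scales, CPET and biomarkers. The Discussion relies on the biomarkers to support the efficacy evaluation, and on two of them (GDF15 and sCD40L) for its argument about prognosis. Leaving the conflict open also leaves a choice between adjusted and unadjusted p-values.

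**Working it through.** **1. The plan's own figure.** The only sample size calculation (2.3.3) is for the binary primary outcome: 45.7% against 69%, two-sided 5%, 80% power. With the unpooled formula, (1.96 + 0.8416)² × (0.457 × 0.543 + 0.69 × 0.31) / 0.233² = 7.849 × 0.4621 / 0.05429 = 66.8, so 67 per group as stated; 67 × 1.1 = 73.7, so 74. It reproduces. It has no bearing on continuous outcomes, for which the article gives no power figure.

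**2. Inputs.**
- From the article: five centres, 1:1 allocation stratified by centre, 148 patients, 134 (2 × 67) evaluable.
- Assumed: the share ρ of total variance lying between centres (0 to 0.20), near-equal centre sizes, a normal outcome, and treatment effects of 0.45 or 0.463 SD. The article gives none of these.

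**3. Analytic standard error ratio.** Set total variance to 1. With balance within centre, the true variance of the difference is proportional to 1 − ρ. With five equal centres, the pooled variance in the t-test is about (1 − ρ) + (4/5)ρ = 1 − 0.2ρ. The ratio of the t-test's standard error to the correct one is √[(1 − 0.2ρ)/(1 − ρ)], and the true size is about 2Φ(−1.96 × ratio).

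| ρ | (1 − 0.2ρ)/(1 − ρ) | SE ratio | approx. size |
|---|---|---|---|
| 0 | 1 | 1.000 | 5.0% |
| 0.02 | 0.996/0.98 | 1.008 | 4.8% |
| 0.05 | 0.990/0.95 | 1.021 | 4.5% |
| 0.10 | 0.980/0.90 | 1.043 | 4.1% |
| 0.20 | 0.960/0.80 | 1.095 | 3.2% |

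**4. Simulation A:** 134 patients, balanced within centre, 20,000 runs per setting, effect 0.45 SD for power.

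| ρ | size, t-test | power, t-test | power, model with centre |
|---|---|---|---|
| 0 | – | 73.7% | 73.5% |
| 0.05 | 4.6% | 74.0% | 75.3% |
| 0.10 | 4.0% | 74.6% | 77.4% |
| 0.20 | 3.2% | 77.1% | 82.4% |

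At ρ of 0.05 to 0.20, the model with centre had size 4.8-4.9%.

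**5. Simulation B:** 148 patients in centres of 30, 30, 30, 29 and 29, blocks of 4 (an assumption), 20,000 null runs, and 6,000 runs at 0.463 SD.

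| ρ | size, t / model | SE ratio | power, t / model |
|---|---|---|---|
| 0 | 5.0% / 4.9% | 1.00 | 79.4% / 79.4% |
| 0.02 | 4.7% / 4.9% | 1.01 | 79.9% / 80.5% |
| 0.05 | 4.6% / 4.9% | 1.02 | 80.9% / 82.0% |
| 0.10 | 4.4% / 5.2% | 1.04 | 81.9% / 84.4% |
| 0.20 | 3.5% / 5.1% | 1.09 | 83.9% / 88.2% |

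Rank tests behave alike. The size of Mann-Whitney against the centre-stratified van Elteren test was 4.9% / 4.8% at ρ = 0, 4.2% / 5.1% at 0.10 and 3.5% / 5.2% at 0.20.

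The formula and both simulations agree on direction and closely on size. B is slightly milder at the larger shares, as one would expect when unfinished blocks leave a centre not quite balanced.

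**The case against.** **The tests do have stratified forms.** A reader might infer that continuous outcomes cannot be stratified by centre under this plan. That goes too far. Van Elteren is the stratified Mann-Whitney test, a linear model with centre is the stratified counterpart of the t-test, and CMH has a mean-score form for ordinal or continuous responses. What stands is that the article invokes none of these for continuous data, and that mean-score CMH would give a p-value without a mean difference and interval.

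**The intent to stratify is stated.** The article says that "analyses will be stratified by study site" and does not limit CMH to categorical outcomes. It is therefore not established that the final analysis will ignore centre, and the detail could sit in an unseen analysis plan. That is fair, but the point is not about missing detail: the article does name tests for continuous data, and they do not fit its own stratification sentence.

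**Least-squares means come from a model.** So it is not shown that every interval would be too wide. This stands as a limit. But the sentence belongs to the paragraph on baseline imbalance, where the model is optional and centre is not named.

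**CPET may be less exposed than it looks.** The article describes mitigation, and its CPET outcome is improvement, measured before and after treatment. A fixed additive offset at a centre would cancel in a change score. That is correct; centre differences in scaling or in the change itself would not cancel. CPET should not be taken as a proven worst case.

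**Conclusion.** The concern holds as an unreconciled choice of method with a conditional cost. For continuous outcomes, section 2.7 names unstratified tests beside a requirement to stratify by site, and no other sentence resolves it.

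The cost depends on between-centre variance, for which the article gives no figure: nil if centres do not differ; about one point of power or less, up to 1.3 points between the two simulations, at a share of 2-5%; and material only at about 10-20%, where 2.5 to 2.8 points are lost at 10% and 4.3 to 5.3 points at 20%. These figures also assume near-equal centres and normal outcomes.

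A reader might go on to infer inflated false positives, a biased treatment estimate or a weakened primary analysis. None follows. The error is in the conservative direction, balance within centre keeps the comparison unbiased, and the primary outcome is binary and covered by CMH. This is a cheap improvement to the secondary analyses and does not threaten the trial's main conclusion.

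**What to change.** In section 2.7, replace the t-test or Mann-Whitney sentence for continuous efficacy outcomes with wording such as: *Continuous efficacy outcomes will be compared with a linear model containing treatment and centre as fixed effects, on the log scale where skewed, and the adjusted mean difference will be reported with its 95% confidence interval. Where a rank test is needed, the van Elteren test stratified by centre will be used.* State also that centre enters any ANCOVA or logistic model. Settle this before data lock.

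The cost is wording and four degrees of freedom for five centres (residual 146 to 142 with 148 patients). No extra data are needed. With no centre differences, the linear model's power was unchanged in simulation B and 0.2 points lower in simulation A. The van Elteren test is not quite free in that case (76.0% against 77.2% for Mann-Whitney in simulation B), but it gains at larger shares (85.9% against 81.8% at ρ = 0.20). That favours keeping the linear model as the default.
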